## Abstract

**Background:** Recent research has identified neuropsychological disorders, specifically executive function disorders, in premature children. Executive functions support goal-oriented mental activity and play a role in the development of social cognition. This underlies the social and emotional behavior of individuals. Parental anxiety is also an important environmental factor that can influence the psycho-emotional development of children.

**Objectives:** The present protocol aims to compare the development of social cognition in school-age children born prematurely to that of school-age children born full-term, and to determine the impact of executive (dys)function and parental anxiety on such development.

**Methods/Design:** In this cross-sectional protocol, 28 prematurely born children aged 7-10 years (“preterm”) and 28 full-term born children aged 7-10 years (“control”) will be included. The “preterm” and “control” groups will be matched for sex and age. The neuropsychological evaluation will include that of non-verbal intellectual efficiency (Raven's colored progressive matrices), verbal level (WISC-IV subtests), and executive functions (NEPSY II subtests and the opposite worlds of TEA-CH). The evaluation of social cognition will be conducted via tests of the theory of cognitive and affective mind. Several dimensions of the level of parental anxiety will be collected through the Spielberg Trait Anxiety Inventory Form Y, Beck Depression Inventory, Social Support Questionnaire-6, Parental Stress Index and, specifically for mothers, the Modified Perinatal Post-Traumatic Stress Disorder Questionnaire.

**Discussion:** The results of this protocol will aid our understanding of the development of social cognition in premature children and to determine the factors that influence such development. This clinical research project, although following a fundamental approach, will have clinical implications because a more precise description of the development of social cognition in this school-age population will make it possible to better determine the cognitive targets of therapeutic actions and to search for predictive indices of the efficacy of practices.

**Trial Registration:**https://clinicaltrials.gov/ct2/show/NCT03007095, identifier: NCT03007095.

## Introduction

According to the World Health Organization (2013), a child born before 37 weeks of amenorrhea is considered to be premature. Prematurity is strictly defined as a birth before 37 weeks, significant prematurity before 32 weeks, and very significant prematurity before 28 weeks. In France, preterm birth affects 50,000-60,000 children every year (7.4% of live births in 2010 (1). In almost all countries with reliable data, premature birth rates have been increasing for several years. This finding necessitates the study of the development and future of premature children. The literature indicates that such children are more likely to have cognitive and motor disorders, behavioral disorders, and academic problems than are full-term (2) children, with the severity of the disorders largely dependent on gestational age and/or birth weight (3).

In recent years, research has identified neuropsychological disorders, specifically executive function disorders, in premature children, even in so-called “late premature children.” Executive functions are mental processes that are goal-oriented and allow for an adaptive response to the environment. Three sets of executive functions are generally considered (4): inhibition, working memory, and cognitive flexibility. Inhibition refers to the ability to resist and not act impulsively, thereby integrating attentional control. Working memory refers to the ability to mentally maintain and process information. Flexibility is the ability to alter one's perspective in response to changes in the environment and, in a complementary manner, to maintain a mental perspective when the environment is irrelevant. Some authors describe these executive functions (4, 5) as basic elements necessary for the implementation of other so-called superior executive functions: reasoning, problem solving and planning (4–6). A growing body of research indicates the difficulties experienced by premature children in tasks that require such executive functions (7). It should be noted, however, that this research is not consensual as to which executive functions are most affected by the degree of prematurity. Indeed, while some authors observed a lack of cognitive flexibility, working memory, and inhibition (8) in very significantly premature children aged 4–12 years compared to that in children born full-term, other authors found differences only in cognitive flexibility between very significantly premature children aged 2 years old (9) or 8–12 years old (10) and children born full-term, without any impact on working memory and inhibition.

The impact of such executive dysfunction on the development of premature children is poorly understood. Few studies have related this dysfunction to academic performance (11–15), and no research has linked such executive dysfunction to social cognition. Social cognition is the study of the cognitive processes that underlie the social and emotional behavior of individuals (16). Social cognition thus integrates different skills, including the ability to understand the emotional and cognitive mental states of others, which are known as the affective and cognitive theories of mind. The literature on the development of full-term children highlights the role of executive functions in the development of these theories of mind, both cognitive (17) and affective (18). In large syntheses such as those by Schneider et al. (19) or Nader-Grosbois et al. (20) hypothesize links between the development of executive functions such as auditory attention, inhibition or shifting and the construction of theories of mind (notably affective with false beliefs). It is therefore prudent to query whether premature children, because of their executive dysfunction, atypically develop the theories of the mind, which is a key concept in social cognition. There is little literature on this subject, despite children born very significantly prematurely often being described as having difficulties in social relations (21). Only the study by Jones et al. (22) attempted to answer this question, but did not yield any convincing results with regard to the cognitive theory of mind.

Finally, the anxiety level of the mother and, more broadly, of the parents is known to impact the development of the premature child (23). According to Guralnick (24), the premature child would be exposed to the “double-stress” of parental care and anxiety and would therefore be twice as vulnerable. The child's developmental trajectory would then endure the direct effects of neurodevelopmental immaturity and the indirect effects linked to the tryptic stress/anxiety/depression mediated by daily interactions with parents. Singer (25) and Pierrehumbert (26) confirmed this hypothesis and highlighted a correlation between maternal psychopathologies (anxiety, depression) and the child's state of health. It therefore seems essential to consider the effect of this contextual aspect on the development of the child's social cognition.

## Objectives

### Main Objective

The main objective of this protocol is to compare the development of the theories of mind (affective and cognitive) in school-age children born prematurely to those of school-age children born full-term.

### Secondary Objectives

The secondary objectives will be (1) to study the association between the executive functioning and theories of mind of school-age children and (2) to study the association between parental anxiety and theories of mind of school-age children.

## Hypotheses

A developmental delay or deficit in the theory of mind in school-age children born prematurely compared to that in school-age children born full-term is expected. This delay or deficit is thought to be related to executive dysfunction and/or the level of parental anxiety.

## Methods

### Ethical Approval

This protocol was approved by the Ethics Committee of Nancy Est III (12/06/2016) and by the French Agency for Medicines and Health Products (08/18/2016). The protocol will be conducted according to the principles of the Declaration of Helsinki and in line with the Guidelines for Good Clinical Practice.

### Protocol Design

This is a cross-sectional protocol of the preterm/control type.

### Participants and Procedure for Recruitment

The subjects will be children born at the maternity ward of the CHU de Reims, France (Reims University Hospital). Information will be given by telephone to caretakers by a clinical research assistant. Once the parent or legal guardian of the children consent to participate in the study, written informed consent will be obtained from the parent or legal guardian of the children. Both the child and the parents or legal guardian must provide their consent for the child's participation in the study.

A total of 28 children born prematurely at the Reims University Hospital, aged 7-10 years (“preterm”), and 28 children born full-term at the Reims University Hospital, aged 7-10 years (“control”), will be included. The “preterm” and “control” groups will be matched for sex and age (± 3 months).

The inclusion criteria are as follows:

“Preterm” children: (1) Children born prematurely (before 37 weeks), making a clear distinction between high and medium preterm infants, (2) aged 7–10 years at the time of inclusion, and (3) enrolled in a non-specialized primary school;

“Control” (full-term) children: (1) Children born at ≥37 weeks, (2) aged 7–10 years, and (3) enrolled in primary school.

“Preterm” and “Control” children: (1) Children and parents affiliated with a social security system, and (2) holders of parental authority will have signed an informed consent form.

The exclusion criteria for the “preterm” and “control” children are as follows:

*Related to the child:* (1) Children with intrauterine growth restriction, (2) multi-pregnancy children, (3) children with organic malformation, (4) children with genetic abnormalities, (5) children with neuro-motor pathology, (6) children with overall developmental delay (IQ of <80), and (7) children refusing to participate in the study.

*Related to the parents:* (1) Minor parents, (2) parents with a proven intellectual deficit, (3) parents with acute or chronic psychotic disorders, (4) parents with difficulties in understanding and speaking the French language, (5) parents under a protective regime (guardianship or curatorship), and (6) parents refusing to participate in the study.

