#### Sample Size

Because of lack of literature, sample size calculation could not be performed on association between theories of mind and prematurity. Because of link between verbal skills and TOM has been shown in several studies that highlighted the impact of verbal skills on TOM task performance (47, 48), the calculation of the number of subjects required was performed for association between prematurity and WISC VCI with the following hypotheses: an average VCI score for “control” patients of 103.2 ± 12.6 (49) and an average VCI score for “preterm” patients of 92. With an alpha risk of 5%, a power of 90%, and a bilateral test, the number of patients required was 28 per group (NQuery software version 4.0).

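### The school-type restriction is written for preterm children only, so some children in specialised schooling could enter the control group but not the preterm group

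*Protocol article*

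**What the plan says.** The Protocol article lists inclusion criteria separately for the two groups under Participants and Procedure for Recruitment. The third preterm criterion is to be "enrolled in a non-specialized primary school". The parallel control criteria read "2) aged 7–10 years, and (3) enrolled in primary school". The qualifier on type of school is absent for controls, and the article does not explain the difference.

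One exclusion list then covers both groups: "The exclusion criteria for the “preterm” and “control” children are as follows". It includes "children with overall developmental delay (IQ of <80" and "children with neuro-motor pathology", as well as genetic abnormality and organic malformation. It does not mention behavioural, learning or social-communication disorders.

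On matching, the article says only that the "groups will be matched for sex and age (± 3 months". The child data listed under Socio-Demographic Data include school level but do not name type of school. The Statistical Analysis section does not name it as a factor either.

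**The concern.** The main objective is a direct comparison of theory of mind between preterm and full-term children, so both groups should be recruited under the same rule apart from gestational age. Type of school is unlikely to be neutral for this outcome, because children may be placed in specialised schooling for the kind of cognitive, behavioural or social difficulty that the study examines.

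If that restriction is applied to one group only, part of the observed difference reflects recruitment and not prematurity. The hypothesis is a delay or deficit in preterm children. Admitting lower-scoring controls while barring their preterm counterparts would work against finding it and would make a null result harder to interpret.

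**Working it through.** **1. The plan's own figure, used here only for scale.** The Sample Size section assumes "an average VCI score for “control” patients of 103.2 ± 12.6" and a preterm mean of 92, with two-sided alpha 5% and power 90%.

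- Difference: 103.2 − 92 = 11.2 points. Standardised: 11.2/12.6 = 0.89 SD.
- Normal approximation: n = 2(1.960 + 1.282)²/0.889² = 26.6, so 27 per group.
- Two-sample t-test: power is 0.893 at 27 per group and 0.904 at 28.

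The stated 28 per group is reproduced, and nothing in this point changes it.

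**2. Who is treated differently.** Take a child in specialised schooling and read the criteria literally.

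| Child in specialised schooling | If preterm | If full-term |
|---|---|---|
| IQ below 80, or neuro-motor, genetic or malformation exclusion | Excluded (shared list) | Excluded (shared list) |
| IQ 80 or more and no shared exclusion | Ineligible (third inclusion criterion) | Eligible |

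Only the second row is asymmetric.

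The shared IQ rule does act on both groups. As an illustration, let verbal comprehension stand in for IQ and assume normality with SD 12.6 in each group. The rule then removes Φ((80 − 103.2)/12.6) = 3.3% of potential controls and Φ((80 − 92)/12.6) = 17.0% of potential preterm children.

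**3. Size.** The documents give neither the frequency of specialised schooling nor the theory-of-mind scores of such children, so the inputs below are assumptions. If k of the 28 controls are in specialised schooling and score on average g SD below the other controls, the control mean falls by k × g/28.

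| k | g (SD) | Fall in control mean |
|---|---|---|
| 1 | 1 | 1/28 = 0.04 SD |
| 1 | 1.5 | 1.5/28 = 0.05 SD |
| 1 | 2 | 2/28 = 0.07 SD |
| 2 | 2 | 4/28 = 0.14 SD |

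The third row is 0.07/0.89, about 8% of the planned standardised difference. The standard error of a difference between two groups of 28 is √(2/28) = 0.27 SD, so a shift of 0.07 SD is about a quarter of one standard error.

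These are shifts in means. The planned univariate group comparison is a Wilcoxon test, in which one control enters 28 of the 28 × 28 = 784 preterm-control pairs (3.6%). A single very low score therefore has bounded influence there.

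**4. Whether anything else in the plan corrects it.** Matching on sex and age does not. Adjustment for type of school is not named. The follow-up items collected for the child (for example speech therapy, psychological or child psychiatry follow-up) might identify some of these children, but no use of them for this purpose is stated.

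**The case against.** The strongest reply is that the control line is shorthand. The preterm line also ties age to the time of inclusion and the control line does not, yet nobody would take that as two age rules. The article condenses a fuller protocol that is not shown, and ordinary primary school may be meant for both groups. This is a fair reading, and it rules out any claim that a one-sided design was intended. It does not remove the point: both criteria are printed, they differ, and a recruiter who follows them could apply different rules.

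Second, the shared exclusions take out the main low-functioning groups on both sides. That stands, and it confines the concern to the second row of the first table in the working.

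Third, full-term children in specialised schooling who pass every shared exclusion are probably rare, so the expected shift may be well below the 0.07 SD shown for one such child. That also stands.

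Fourth, any bias would be towards no difference and could not create a false preterm deficit. This holds if children in specialised schooling score lower, which is plausible but assumed. It lessens the harm without removing it, because a null result would still be open to question.

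**Conclusion.** The schooling criterion differs between the groups without a stated reason. Followed literally, children in specialised schooling with an IQ of 80 or more and no shared exclusion can enter the control group only. The likely effect is to narrow the difference in theory of mind. Its size cannot be derived from the documents and is probably small: about 0.07 SD for one such control at −2 SD. The direction rests on the assumption that these children score lower.

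Two stronger readings are tempting and are not supported.

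- A reader might infer that low-functioning children are removed from the preterm group only. They are not: the IQ, neuro-motor, genetic and malformation exclusions apply to both groups.
- A reader might also count the preterm children lost to the school rule. If 5% to 10% were lost and scored 1.5 SD lower, the preterm mean would rise by 0.05 × 1.5 = 0.075 to 0.10 × 1.5 = 0.15 SD, and adding 0.07 SD for a control would suggest a total of about 0.15 to 0.2 SD. All these inputs are assumed. The two parts also refer to different target populations: the first is a bias if all eligible children are the target, the second if only mainstream pupils are. They should not be added. The first part also remains once the criteria are aligned on mainstream schooling, so it is a limit on generalisation and not a cost of the unequal wording.

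**What to change.** Give the control group the same third criterion as the preterm group, "enrolled in a non-specialized primary school", and limit the conclusions to children in mainstream schooling. If the difference is intended, state the reason.

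If recruitment has begun, record the type of school of every control already included, report it, and add a sensitivity analysis of the group comparison that excludes any control in specialised schooling.

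The change is one phrase. It may cost a very few potential controls. Even if a control and the matched preterm child were both dropped without replacement, power for the verbal comprehension comparison would go only from 0.904 at 28 per group to 0.893 at 27. The sample size and alpha stay as they are.

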### Study Interventions

As shown in Table 1, participation in the study will consist of two visits by psychologists or psychiatrists trained at various assessment scales. Data collection for parents will be carried out during the first visit. Data collection for children will be carried out over the two visits. The adoption of two visits for the children will allow for better conditions for the passing of the different evaluation scales and will also improve the children's comfort.

**Table 1 T1:** Protocol design.

	**Visit 1**	**Visit 2**
**Enrollment**		
Eligibility screen	X	
Informed consent	X	
Clinical data record	X	
**Caretakers evaluation**		
STAI: state-trait anxiety inventory	X	
BDI: beck depression inventory	X	
PSSQ: perceived social support questionnaire	X	
mPPQ: modified perinatal post-traumatic stress disorder questionnaire	X	
PSI: parental stress index	X	
**Child evaluation (“premature” and “control”)**		
Vocabulary (WISC-IV)	X	
Similarities (WISC-IV)	X	
Same and opposite worlds (TEA-CH)	X	
Auditory attention (NEPSY-II)	X	
Cognitive theory of mind	X	
Raven's colored progressive matrices		X
Repetition of sentences (NEPSY-II)		X
Affective theory of mind		X

### Outcome Measurements

#### Neuropsychological Evaluation of Exposed and Unexposed Children

The neuropsychological evaluation will analyze the children's non-verbal intellectual efficiency, their verbal level, and their executive functions (attention, inhibition, flexibility, and working memory).

##### Raven's Colored Progressive Matrices

This test evaluates non-verbal intellectual efficiency by measuring reasoning capacity by analogy. It has the advantage of not being sensitive to socio-cultural elements within the same ethnic group. The color version for children (27) has 36 questions grouped into 3 sets of 12 questions each, of increasing complexity.

##### Verbal Subtests of the WISC-IV

The “similarities” and “vocabulary” subtests of the WISC-IV (28) allow for an extrapolated verbal comprehension index (eVCI) to be calculated. This choice entails to compute a prorata because we only want to assess semantic competences, and not social cognition (or more pragmatic) competences as required by Comprehension subtest. We propose this method in order to focus only on semantic skills competences and to avoid a possible bias in the evaluation of the real skills of the two populations studied in theory of mind assessed through these semantic comptences. The “similarities” subtest includes 23 pairs of words of increasing difficulty and specifically evaluates verbal abstraction. The “vocabulary” subtest contains 24 questions of increasing difficulty for which children must provide a definition.

##### Executive Functions

Auditory attention and repetition of phrases. Using two 3 min word listening tasks, the “Auditory Attention and Associated Responses” subtest of the NEuroPSYchological Assessment 2nd Edition (NEPSY-II) (29) evaluates selective auditory attention and the ability to maintain it, and the ability to modify and maintain a new rule.

The “sentence repetition” subtest evaluates the child's ability to repeat sentences of increasing complexity and length (17 in total). It allows to assess the verbal working memory capacities.

We preferred the NEPSY auditory attention test to the TEA-CH (Elevator counting) because the NEPSY assesses selective auditory attention as well as higher-level executive components that the TEA-CH does not offer.

Inhibition/flexibility. This task from the Test of Everyday Attention for Children (TEA-CH) consists of two tests and evaluates the inhibition and/or cognitive flexibility skills of a child's verbal response (30). In the first test, the “Same World,“ the child must state as quickly as possible the numbers (1 or 2) as they succeed each other in each box of a course provided on a sheet of paper. In the second test, the “Opposite World,” the child must state ”1“ when he sees a ”2“ and state ”2“ when he sees a ”1“ as quickly as possible throughout the course. Four worlds will follow in succession; one same world, two opposite worlds, and finally one same world.

#### Experimental Evaluation of Social Cognition in Exposed and Unexposed Children

Theory of Mind tests are not standardized for the moment, neither in English or French, except for the very simple theory of mind item of the NEPSY-2. Literature on theory of mind is currently based on an experimental approach rather than on a standardized test approach. Our theory of mind assessment is adapted from previous studies. Because of the multiplicity of terms in the field of social cognition – theory of mind implicit, explicit, cognitive, affective- and knowing that it does not cover exactly the same functions, we are interested in what happens between 7 and 10 years old when it comes to articulating the mental states of belief (false belief) or non-intention (false step) to emotions.

